#### Laboratory assessments

2.5.2

Blood samples are obtained at all visits after a minimum of 8 h overnight fasting and processed by the local laboratory using standard methods for routine tests. Participants may take their regular morning medication but are asked not to take any of their diabetes medications in the morning of their study visit.

Furthermore, blood samples are collected for biobanking at most visits and stored at the Biobank of the Medical University of Graz at −80°C.

#### Bioelectrical impedance analysis (BIA)

2.5.3

BIA (BIACORPUS^RX4000^, MEDICAL HealthCare GmbH) is used to determine the distribution of the individual body components (fluids, muscle mass and fatty substance) in the study participants.

#### Nutrition counselling

2.5.4

Nutrition counselling is performed by a professional dietician on site and recommendations and examples for menus on the fasting days are given to the participants.

#### Indirect calorimetry

2.5.5

The resting energy expenditure (REE) is measured by indirect calorimetry (IC) (Cortex, Germany) before and after the study intervention. Oxygen consumption and carbon dioxide production is measured, and energy expenditure is calculated by the Weir formula.^25^

#### Fitness tracking

2.5.6

To assess total energy expenditure, a fitness tracker (movisens GmbH, Germany) is worn continuously on the non‐dominant wrist throughout the intervention period.

#### Questionnaires

2.5.7

All participants of this study are asked to fill out 6 different Questionnaires: (1) the Food Frequency Questionnaire (FFQ), where frequency and portion size of consumption of food items are asked according to specified categories, (2) the International Physical Activity Questionnaire (IPAQ). This tool was developed for measuring physical activity and is used in the current study to record the time spent being physically active in the last 7 days, (3) The Eating Disorder Examination Questionnaire (EDE‐Q) is a 28‐item self report questionnaire, adapted from the semi‐structured interview, the Eating Disorder Examination (EDE). The questionnaire is designed to assess the range, frequency and severity of behaviours associated with a diagnosis of an eating disorder, (4) The Pittsburgh Sleep Quality Index (PSQI) is a self report questionnaire that assesses sleep quality over a 1‐month time interval, (5) Food Craving Inventory is a reliable and valid self‐report measure of general and specific food cravings, (6) The Beck Depression Inventory (BDI), a 21‐item self report rating inventory, is used to measure characteristic attitudes and symptoms of depression, and (7) A questionnaire is used to assess the satisfaction with the CGM system.

Cognitive function test available at cognitivefunctiontest.info provided by Food for Brain (UK) will also be applied.

#### Continuous glucose monitoring (CGM)

2.5.8

CGM (Abbott FreeStyle Libre 2 device, Abbott Diabetes Care, Almeda, CA, USA) is used throughout the intervention phase.

#### Six‐minute walking test (6‐MWT)

2.5.9

The 6‐MWT is performed on an indoor course, and participants are instructed to walk as quickly as possible for 6 min. The distance walked is measured to the closest metre.

#### Oral glucose tolerance test (oGTT)

2.5.10

Participants attend the Cardiometabolic Trials Unit in the morning after an overnight fast. The oral glucose tolerance test (oGTT) is performed at the beginning and at the end of the 12‐week intervention phase. Participants consume 75 g of glucose diluted in 250 mL of water (Glucoral 75 citron, Germania Pharmazeutika, Vienna) within ≤5 min; blood is sampled every 30 min for 2 h. The oGTT is performed after an overnight fast following an eating day (for the IER group alone and the combination group of IER and exercise).

#### Faeces sampling and microbiome analysis

2.5.11

Sampling is performed using stool collection tubes (Sarstedt, Nümbrecht, Germany) at start and end of intervention phase. Bacterial DNA will be extracted from stool samples using the MagNA Pure LC DNA Isolation Kit III (Roche). The 16S rRNA gene will be amplified in a PCR reaction, sequenced with next‐generation sequencing technology (Roche Genome Sequencer FLX or Illumina MiSeq) and analysed by an in‐house R pipeline.

#### Measurements of handgrip strength

2.5.12

Handgrip strength is measured using the JAMAR Hydraulic Hand Dynamometer (Patterson Medical) as an indicator of overall muscle strength and physical function. It is widely recognized as a reliable proxy for total body strength and has been shown to correlate strongly with functional performance across multiple populations.^26^, ^27^

### Investigations in subgroups

2.6

In a subgroup of participants, additional investigations are carried out. These investigations include the MoCA (Montreal Cognitive Assessment) screening, the Symbol Digit Modalities Test (SDMT), BODPOD as an additional method to measure body composition and the Doubly labelled water methods for measuring total energy expenditure. A complete list of the additional investigations can be found in the supplements (Table S2).

### Glycaemic management

2.7

Participants in this randomized clinical trial may start additional non‐randomized medication according to the guidelines of the Austrian Diabetes Association^22^ if HbA1c remains >7.5% (>58 mmol/mol) at visit 3 or 4.

### Statistics

2.8

A detailed statistical analysis plan will be finalized before locking the database. All statistical analyses will be conducted in R version 4.5.2. The primary analysis will be conducted on the ITT population and sensitivity analysis will be conducted in the PP population. In descriptive analysis, continuous variables will be summarized as mean ± SD and categorical variables as frequencies and percentages (%) for the overall trial population and by each trial arm, respectively. The primary outcome of mean change in weight over visits between trial arms will be analyzed using the mixed effects model (MMRM) with an unstructured covariance matrix for modelling within‐subject residuals and considering maximum likelihood estimation under the missing‐at‐random assumption. The MMRM will include intervention groups, visit and intervention‐by‐visit interaction as fixed effects. In addition, baseline body weight, baseline body weight–visit interaction, age, sex, duration of diabetes, use of GLP‐1 receptor agonist and glucose‐lowering medications will be added as adjustment covariates in the MMRM model.

The marginal mean for change in body weight with 95% CIs will be estimated from the MMRM model for each intervention group. Family‐wise error for multiple comparisons will be controlled by employing Dunnett's approach and the fixed sequence gate‐keeping method. In step 1, pairwise comparisons of each active intervention group with the control group will be conducted using a 2‐sided alpha level of 0.05 and Dunnett's adjusted confidence intervals. In step 2, if any intervention group is found to be significantly different from the control group (*p* < 0.05), exploratory pairwise comparisons between active intervention groups will be conducted, and multiplicity adjustment will be carried out using Holm's method. The primary results will also be reported as model‐derived percentage change difference from baseline between intervention groups.

Key secondary outcomes will be analysed using similar statistical modelling, fixed sequence and family‐wise error control strategies. Specifically, change in TIR will be analysed using the MMRM model. The percentage of participants achieving composite outcome of TIR increase (≥5%), body weight reduction (≥3%) and stable or reduced glucose‐lowering treatment over visits will be analysed using generalized estimating equations (GEE) with binomial distribution and identify link function and considering the exchangeable correlation structure. Robust standard errors will be estimated and results will be reported in terms of differences in marginal probabilities and marginal odds ratios along with 95% CIs.

The prespecified subgroup analyses will also be conducted to evaluate the heterogeneity of intervention effect on primary outcome with respect to covariates including duration of diabetes, baseline body weight, GLP‐1 agonist use and HbA1c. For continuous variables, both continuous values as well as relevant cut‐offs will be used. For each subgroup analysis, interaction term for the subgroup variable with intervention will be added in the primary MMRM model and both model estimates with p‐interactions and marginal means for each subgroup will be reported. The subgroup analyses will be exploratory and therefore not be corrected for multiplicity.

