### Sample size estimation

2.3

The sample size estimation is based on the analysis of covariance (ANCOVA) approach and data from our INTERFAST‐2 study that investigated exercise and fasting interventions in people with T2D treated with insulin.^24^ Based on INTERFAST‐2 data, we assumed the mean ± standard deviation body weight of 104 ± 13 kg at baseline, correlation (r) of 0.95 from baseline to follow‐up and the mean difference in weight loss of 5.0 ± 4.1 kg from baseline to follow up between intervention arms. Considering a 2‐sided type 2 error rate of 5% and a power of 90%, a total of at least 60 completers is required (15 in each study arm). The study discontinuation rate is expected to be 15%; therefore, the overall sample size is estimated to be 70 participants but could be higher to satisfy the requirement of 15 completers in each study arm.

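### Primary MMRM by maximum likelihood: without a small-sample adjustment, standard errors are about 5–7% too small at 15 per arm, so REML with small-sample degrees of freedom should be named

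*Protocol article*

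**What the plan says.** Section 2.8 (Statistics) of the protocol article describes the primary model for body weight as an MMRM "with an unstructured covariance matrix for modelling" the within-subject errors, and it names the estimator: "residuals and considering maximum likelihood estimation", under missing at random. "The MMRM will include intervention groups, visit and" their interaction. Baseline weight and its interaction with visit are added, as are "age, sex, duration of diabetes, use of" GLP-1 receptor agonists and other glucose-lowering drugs; these "medications will be added as adjustment covariates in the MMRM model".

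Three active arms are compared with control at a two-sided "alpha level of 0.05" with Dunnett-adjusted intervals. For the arm estimates, "The marginal mean for change in body weight with 95% CIs will be estimated from the MMRM model". R 4.5.2 is the stated software, but no package is named. The time-in-range outcome is also to be analysed by MMRM.

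Section 2.3 (Sample size estimation) fixes the scale of the trial: "at least 60 completers is required (15 in each study arm").

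**The concern.** ML estimates the residual covariance without allowing for the mean parameters fitted from the same data, so the variance is biased downward. The bias grows with the number of mean parameters relative to participants. Here there are few participants and many parameters. Each visit has four arm means and a baseline slope, and at least five further covariate terms are shared across visits.

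If the standard errors are too small, p values are too small and intervals too narrow. The stated family-wise 5% is then exceeded on the primary outcome. The excess carries into step 2, which opens when any step 1 comparison reaches p < 0.05, and into the time-in-range model. The error always favours declaring an effect.

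The estimator is stated in the article, so this is not simply a detail left to the SAP.

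**Working it through.** **1. Inputs from the article (2.3 and 2.8).** Baseline SD 13 kg, correlation 0.95, difference 5.0 kg, SD 4.1 kg, power 90%, 15 completers per arm, 15% discontinuation, and three Dunnett comparisons at 5%. Section 2.3 prints the 5% as a type 2 error rate; it is read here as type 1.

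**2. The plan's own figure.** The ANCOVA residual SD is 13 × √(1 − 0.95²) = 4.06 kg. Per arm, n = 2 × (1.960 + 1.282)² × (4.1/5.0)² = 14.1, so 15 per arm and 60 completers. Then 60/0.85 = 70.6, against the stated 70. The sample size reproduces and is not in question.

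**3. Closed-form guide.** With p mean parameters per visit and complete data, the ML/REML ratio of standard errors is √((60 − p)/60).
- p = 5 (four arms and baseline): √(55/60) = 0.957.
- p = 10 (if five further covariates also acted separately at each visit): √(50/60) = 0.913.

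The further covariates are not crossed with visit, so the planned model should lie between these.

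**4. Simulation under no effect.** The model had an unstructured covariance, arm by visit, baseline by visit and further covariates, with day-84 contrasts against control. Assumed: residual SDs of 2.4, 3.3 and 4.06 kg at the three visits to day 84 (only 4.06 comes from the article) and an AR-type correlation of 0.85. Five covariate terms stand for age, sex, duration, GLP-1 RA use and medications; eight allow for medications coded by class. The t reference has completers − 5 − (number of covariates) degrees of freedom, for example 60 − 5 − 5 = 50. There were 8,000 trials per row (4,000 for six visits), so the Monte Carlo standard error at 7% is √(0.07 × 0.93/8000) = 0.3 points (0.4 for six visits).

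| Setting | SE ratio ML/REML | ML single, t / z (%) | ML Dunnett family, t / z (%) | REML single, t (%) | REML family, t (%) |
|---|---|---|---|---|---|
| 15 per arm, 3 visits, 0 further covariates | 0.957 | 5.8 / 6.4 | 6.3 / 7.1 | 4.8 | 4.8 |
| 15 per arm, 3 visits, 5 covariates | 0.942 | 6.7 / 7.4 | 7.0 / 8.2 | 5.1 | 5.3 |
| 15 per arm, 3 visits, 8 covariates | 0.932 | 6.6 / 7.3 | 7.5 / 8.7 | 5.0 | 4.8 |
| 15 per arm, 6 visits, 5 covariates | 0.943 | 6.9 / 7.5 | 7.5 / 8.9 | 5.5 | 5.6 |
| 18 per arm, 15% dropout, 3 visits, 5 covariates | 0.950 | 6.3 / 7.0 | 6.5 / 7.6 | 5.1 | 4.9 |

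With five covariates and three visits, an unadjusted 95% interval for a difference from control covers 100 − 6.7 = 93.3% (t) or 100 − 7.4 = 92.6% (z).

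**5. Other assumed SDs and correlations.** With SDs of 2.0, 3.1 and 4.06 kg and correlations of 0.70–0.88, the SE ratios were 0.948 (5 terms, 4,000 trials) and 0.941 (8 terms, 2,500 trials). The ML family-wise error was 6.8% and 7.9% at the t critical value of 2.41, and 7.6% and 9.0% at the normal value of 2.349. REML at 2.41 gave 5.0% and 5.8%.

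**6. Does REML alone suffice?** No. With a normal critical value, REML still gave a family-wise error of 5.8–6.3% in the settings of step 4.

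**7. An ML fit that rescales.** nlme::gls multiplies the ML standard errors by √(N/(N − p)), with N observations and p fixed effects. For three visits and five covariates, N = 60 × 3 = 180 and p = 3 × 5 + 5 = 20. So √(180/160) = 1.061, and 0.942 × 1.061 = 0.999. In 3,012 null trials fitted this way (R 4.3.3, the SDs and correlation of step 4), the ML/REML ratio was 0.999. Single-comparison error was 5.1% for both, and family-wise error at 2.41 was 5.6% (ML) and 5.5% (REML).

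**The case against.** The strongest reply is step 7. The article fixes R but no package, and at least one common R route, run by ML exactly as written, gives essentially the REML error rates. A reader might infer from the words of section 2.8 that the 5% level and the 95% intervals do not hold. The document does not support so flat a statement, because the outcome depends on an implementation that it leaves open. This reply stands. Its limits are that it was tested in R 4.3.3 rather than 4.5.2, that other packages were not tested, and that an analyst following the text could equally use a fit without the rescaling.

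A reader might also take 8–9% as the family-wise error rate. At 15 per arm that needs a normal critical value, which the article does not state; the 9.0% figure also needs eight covariate terms, and coding medications by class is an assumption.

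The wording may be shorthand for a likelihood method that handles missing data, with REML intended. The degrees-of-freedom method is ordinary SAP content, and its absence here is no fault. Both points are fair. What remains is that ML and REML are different options in R, and the text names the less suitable one. Missing at random gives no reason to prefer ML, since REML is valid under the same assumption.

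Finally, the practical effect is limited. Ignoring covariates, the standard error of a contrast is 4.06 × √(2/15) = 1.48 kg. The Dunnett half-width is 2.41 × 1.48 = 3.57 kg, or 3.57 × 0.942 = 3.36 kg under unadjusted ML. Only a correct t between 2.41 × 0.942 = 2.27 and 2.41 would change verdict. The planned 5 kg difference corresponds to 5/1.48 = 3.4.

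**Conclusion.** The concern holds in conditional form, and its severity is moderate; it is not a must-fix. If the primary MMRM is fitted by ML without a small-sample adjustment, its standard errors are about 5–7% too small at the planned size and covariate load. With a t reference, type 1 error is then about 6.5% for one comparison and about 7–7.5% for the Dunnett family, instead of 5%. The 7.9% in step 5 is within simulation error of that range.

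The direction follows from the method. The size rests on the assumed residual SDs, correlations, number of visits and covariate coding. An ML fit with rescaled standard errors largely escapes the problem, so the defect is that the text permits the inflation, not that it makes it certain.

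**What to change.** In section 2.8, and in the SAP before it is finalized, replace maximum likelihood by restricted maximum likelihood (REML) with Kenward-Roger or Satterthwaite degrees of freedom. Base the Dunnett critical values and intervals on those degrees of freedom. Apply the same to the time-in-range MMRM. If REML was intended all along, the change only corrects the wording.

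The cost is intervals about 5–7% wider than unadjusted ML would give (1/0.950 = 1.05 to 1/0.932 = 1.07), which is their proper width. No further participants or data are needed, and the missing-data assumption stays the same.

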## Abstract

**Aims:**

Lifestyle modification, including caloric restriction and exercise, is fundamental in the treatment of people living with overweight and type 2 diabetes mellitus (T2D). The overall aim of lifestyle intervention schemes is to reduce body weight and improve glycaemic control to reduce the future risk of diabetes‐associated complications. The aim of this study is to determine whether intermittent energy restriction, exercise or their combination is best suited for reaching these targets in individuals with T2D not treated with insulin.

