Although previous studies have demonstrated beneficial effects of dietary restrictions and exercise individually in people with T2D, data on the combined impact of an IER regimen and physical activity compared with each lifestyle intervention alone remains scarce.^21^ Understanding the interaction between exercise and intermittent energy restriction is therefore crucial in order to find the best lifestyle intervention strategies. Hence, the aim of this ongoing study is to assess the safety and efficacy of IER, structured exercise and their combination in people living with overweight/obesity and T2D.

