### Study hypothesis

2.1

Caloric restriction and exercise are keystones of anti‐hyperglycaemic therapy. We hypothesize that the combination of both interventions is safe and most effective for bodyweight reduction and HbA1c lowering in people living with overweight and T2D (Figure 1).

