One can argue that combining a time‐restricted eating and a caloric restriction component to the chosen dietary intervention will not allow one to separate out if a potential beneficial effect is due to one or the other. However, this is not the intention of the current study, which focuses on the changes in clinically relevant outcomes of a simple‐to‐follow dietary intervention rather than in‐depth mechanistic investigations.

The INTERFAST‐3 trial aims to investigate the interplay between IER and exercise in individuals with non‐insulin‐treated T2D, thereby helping to find the best tailored lifestyle intervention for each individual living with T2D.

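### The hypothesis that the combination is most effective, and the aim of studying the interplay, have no confirmatory test: comparisons of the combination with its components are labelled exploratory

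*Protocol article*

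**What the plan says.** Study hypothesis (2.1): "We hypothesize that the combination of both interventions is safe and most effective for bodyweight reduction and HbA1c lowering". The abstract's aim is to "determine whether intermittent energy restriction, exercise or their combination is best suited for reaching these targets". The Introduction says "Understanding the interaction between exercise and intermittent energy restriction is therefore crucial", and the closing paragraph of the Discussion says the trial "aims to investigate the interplay between IER and exercise".

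The arms under Randomization (2.2.3) are IER, exercise, both, and neither, allocated equally.

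Statistics (2.8) fixes the testing order for the primary outcome:
- **Step 1:** each active arm against control, at two-sided 0.05 with Dunnett adjustment.
- **Step 2:** opened if any active arm differs significantly from control. Then "exploratory pairwise comparisons between active intervention groups will be conducted", with Holm adjustment. With three active arms there are three such pairs.

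The model carries a four-level group factor. The only interactions stated for it are with visit and, in the subgroup analyses, with baseline covariates.

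**The concern.** The hypothesis is about the combination relative to its components. Step 1 is about each arm relative to doing nothing. Step 1 can succeed in full while the combination is no better than IER or exercise alone.

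The two comparisons that carry the hypothesis are made, but the plan itself gives them exploratory status. Their gate is also not tied to the combination: exercise alone beating control would open it, even if the combination had failed. The interplay, a declared aim, has no stated estimate.

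At stake is the headline. A report could claim confirmatory success and go on to say that the combination is best, although the plan gives that second statement no confirmatory standing.

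**Working it through.** **Inputs.** From Sample size estimation (2.3): baseline SD 13 kg, correlation 0.95, difference 5.0 kg with SD 4.1 kg, 90% power, 15 completers per arm. I read the 5% error rate as type 1.

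**The plan's own figure.** n per arm = 2 × [4.1 × (1.960 + 1.282) / 5.0]² = 14.1, so 15. This reproduces the plan (power 91.6% by normal approximation, 89.7% by t with 28 df). It is the size for one unadjusted pairwise comparison.

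**Precision.** ANCOVA residual SD = 13 × √(1 − 0.95²) = 4.06 kg. Error df = 60 − 4 arms − 1 covariate = 55, and t = 2.004.

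| Contrast | SE | 95% CI half-width |
|---|---|---|
| Any pair, e.g. combination − IER | 4.06 × √(2/15) = 1.48 kg | 2.97 kg |
| Marginal effect of IER or of exercise | 4.06 × √(1/15) = 1.05 kg | 2.10 kg |
| Interaction: combination − IER − exercise + control | 4.06 × √(4/15) = 2.10 kg | 4.20 kg |

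**Can step 1 succeed when the hypothesis is false?** Set all three active arms 5 kg below control. Each step 1 comparison has 5/1.48 = 3.37 standard errors against a simulated Dunnett critical value of 2.42. All three succeed together in about 66% of simulated trials.

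**Power for combination better than both components.** These are simulations with the same SD and n. Mean changes are listed as control / exercise / IER / combination.

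| Scenario (kg) | Planned step 2, Holm over three pairs | Both at two-sided 0.05 |
|---|---|---|
| 0 / −5 / −5 / −10 | about 76 to 77% | about 85% |
| 0 / −2 / −5 / −7 | about 19% | about 26% |

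The 5 kg difference is the plan's figure. The 2 kg step and both sets of arm means are assumptions.

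**Interaction.** For a 5 kg interaction the noncentrality is 5/2.10 = 2.38, which gives about 65% power.

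**Family-wise error if the two comparisons become one claim.** The claim needs both comparisons to favour the combination at two-sided 0.05, so its own false-positive rate is at most 0.025. Suppose the claim is false and the combination truly beats control. Then at least one component also beats control, and at most one step 1 null can be true. The Dunnett value of 2.42 on 55 df is a per-comparison level of about 0.019, and 0.019 + 0.025 = 0.044, within 0.05. If the combination does not beat control, a false claim first needs a false step 1 rejection, which Dunnett already covers. If instead each comparison could be declared separately at two-sided 0.05, the error could reach 1 − 0.981 × 0.95 = 0.068.

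**The case against.** **The hypothesis is already tested.** A reader might infer that it is left untested. It is not: step 2 compares the combination with each single arm under Holm control. What remains is the exploratory label and a gate that any arm can open.

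**The aim is also stated in a way that step 1 answers.** The last sentence of the Introduction speaks of the safety and efficacy of the three interventions, and Study design calls the trial parallel-arm, never factorial. That is fair, and it is why restating the hypothesis is an acceptable alternative. It does not remove 2.1 or the closing aim.

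**Factorial contrasts are no shortcut.** A reader might infer that marginal effects would answer the hypothesis from the same data with far more power: about 47% for a 2 kg marginal exercise effect against about 20% for combination versus IER in the Holm step. These figures differ in both estimand and adjustment. Take assumed changes of 0 / −4 / −5 / −5 kg, so that exercise adds nothing to IER. The marginal exercise effect is still (4 + 0)/2 = 2 kg and is again significant in about 47% of trials. The interaction is 4 kg and, at the same ratio to its SE, would flag the problem no more often. Marginal effects bear on the hypothesis only under rough additivity. Nor is the pairwise contrast the least precise one; the interaction is.

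**IER versus exercise is not surplus.** Dropping it would conflict with the abstract's aim of finding which option is best suited.

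**The SAP is not shown.** It may add contrasts, so the most that can be said is that none is stated in the article. The status of the step 2 comparisons, however, is stated there and does not depend on the SAP.

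**Conclusion.** The mismatch stands. The stated hierarchy is confirmatory only against control, while the hypothesis is about the combination against its components and a declared aim is their interplay. Step 1 can succeed in full in about 66% of trials in which the combination adds nothing, if all active arms lose 5 kg more than control.

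The gain from correcting this is mainly in what may be claimed. Power for the joint claim rises from about 76 to 77% to about 85% at 5 kg differences, and from about 19% to about 26% in the 2 kg scenario. The trial remains weak for small added benefits and for the interaction.

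The figures assume equal residual SD of 4.06 kg in all arms, 15 completers per arm and no gain from further covariates. The documents do not support saying that the hypothesis goes untested, or that a factorial analysis would settle it.

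**What to change.** In the SAP, from the same MMRM at Visit 5:

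1. Make combination versus IER and combination versus exercise a prespecified hypothesis test. Open it only when the combination beats control in step 1, and write down how alpha passes so that family-wise error is kept. One way is a single joint claim, each comparison at two-sided 0.05 in favour of the combination. Claim that the combination is most effective only if both succeed. Otherwise, restate the hypothesis to match step 1.
2. Keep IER versus exercise as an exploratory comparison.
3. Report the interaction contrast (combination − IER − exercise + control) with its 95% CI as an estimate, and state its imprecision: half-width about 4.2 kg, about 65% power even for 5 kg. Marginal effects may stand beside it as supportive only.

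**Cost:** a few sentences and contrast statements, with no new participants, data or model. The protocol says the SAP is finalised before database lock. With 65 participants randomised by 4 November 2025, the hierarchy is easier to change than the design. The downside is modest power for the joint claim and an imprecise interaction estimate, both of which should be disclosed.

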### Outcomes

2.4

The primary outcome of this study is the change in body weight from baseline to end of the intervention phase (i.e., 12 weeks). Key secondary outcomes comprise change in Time In Range (TIR) [70─180 mg/dL; 3.9─10.0 mmol/L] from baseline to end of intervention and change in the composite of improvement in TIR of at least 5%, weight reduction of at least 3% and stable or reduced glucose‐lowering treatment at end of intervention. Safety endpoints include difference in the number of severe adverse events and differences in TBR1 [54─<70 mg/dL; 3.0─<3.9 mmol/L] and TBR2 [<54 mg/dL; <3.0 mmol/L].

The full list of exploratory secondary outcomes can be found in Table S1.

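### If the composite's identity-link model is covariate-adjusted, it will usually not fit at about 15 per arm; a logit link with standardization gives the same two measures

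*Protocol article*

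**What the plan says.** Section 2.8 (Statistics) sets out an MMRM for change in body weight. Its adjustment terms are "baseline body weight, baseline body weight–visit interaction, age, sex, duration of diabetes, use of GLP‐1 receptor agonist and glucose‐lowering medications". Baseline HbA1c is not among them.

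The same section then turns to the two key secondary outcomes: "Key secondary outcomes will be analysed using similar statistical modelling". For TIR, "change in TIR will be analysed using the MMRM model". The composite requires a TIR gain, a weight loss and, in the words of section 2.4, "stable or reduced glucose‐lowering treatment at end of intervention". It gets a binomial GEE with "identify link function and considering the exchangeable correlation structure"; the printed word is read here as identity. Robust standard errors are planned, and results are to be given as "differences in marginal probabilities and marginal odds ratios along with 95% CIs".

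No covariates are named for TIR or the composite, and no fallback is given for a model that does not fit. HbA1c enters the analysis text only in the subgroup analyses of the primary outcome, among "covariates including duration of diabetes, baseline body weight, GLP‐1 agonist use and HbA1c". Section 2.8 announces a detailed SAP before database lock.

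**The concern.** With an identity link, each participant's response probability is a straight-line sum of arm effect and covariate effects, and nothing holds that sum between 0 and 1. With continuous covariates such as age, diabetes duration and weight, and about 15 participants per arm, some fitted values readily cross a boundary. The binomial variance is then not valid and the fit may stop without converging. The composite is one of only two key secondary outcomes, and an adjusted analysis on the stated link might give no usable result. A link chosen after such a failure would look data-driven.

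The second, smaller matter is TIR. The only covariate list was written for body weight. Table 1 starts CGM at Visit 2, the randomization visit, so the schedule shows no TIR from before randomization. Baseline HbA1c is then the natural glycaemic covariate, and leaving it out gives up some precision.

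**Working it through.** **The plan's own figure.** Section 2.3 gives a baseline SD of 13 kg, r = 0.95, a difference of 5.0 kg, 5% two-sided error and 90% power. The ANCOVA SD is 13 × √(1 − 0.95²) = 4.06 kg. The normal formula gives 14 per arm and the noncentral t gives 15 (power 90.2%), as stated. With 15% dropout, 60 / 0.85 = 70.6, so 71 against the stated 70. The sample size reproduces and is not touched by this point. It fixes about 15 per arm as the setting.

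**Composite: the two links.**
- Identity: p = α + arm effect + Σβx. This must lie in 0–1 for every participant.
- Logit: p = 1 / (1 + exp(−η)), with η the same sum. This always lies in 0–1.

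The article gives no response rates, drug uptake or covariate effects, so all of these are assumed. Each row below comes from simulated trials with 15 per arm. The full list means the weight-model covariates without HbA1c.

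| Model | Visits | Identity: failed or outside 0–1 | Logit: failed |
|---|---|---|---|
| Arm only (control 10–25%, active 25–70%) | day 84 | 2–22% | 2–22% |
| Arm only (control 5–10%, active 25–60%) | day 84 | 3–17% | not run |
| Arm only (same rates) | three | 25% and 52% | not run |
| Arm + baseline weight | day 84 | 27–72% | 4–36% |
| Arm + baseline weight | three | 55% | 21% |
| Full list, same trials for both links | day 84 | 85–100% | 3–20% |
| Full list (drug uptake 25–75%) | day 84 | 88–100% | not run |
| Full list | three | 95% | not run |

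In the like-for-like row, every logit failure came from a trial in which an arm had no responders or only responders. In the three-visit row with baseline weight, 21% of trials had such an arm-by-visit cell, the same share as the logit failures. The identity failures do not depend on an empty arm: in one set of day-84 trials with six covariates, 78–91% of trials had a bad identity fit with no empty arm.

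**How often an arm is empty.** P(no responder among 15) = (1 − p)^15. For p = 10% this is 0.9^15 = 0.206; for p = 20% it is 0.8^15 = 0.035.

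**Can logit deliver the promised measures?** Yes. For arm a, average the fitted probability over all participants with arm set to a, giving p_a. The risk difference is p_a − p_0 and the marginal odds ratio is [p_a / (1 − p_a)] / [p_0 / (1 − p_0)].

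**TIR: gain from baseline HbA1c.** Let r be the partial correlation of HbA1c with the TIR outcome given the other covariates (assumed). The gross cut in standard error is 1 − √(1 − r²). The net cut is from 6,000 simulated ANCOVAs with 60 completers, four arms and seven other covariates.

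| r | Gross | Net |
|---|---|---|
| 0 | 0% | −1.2% |
| 0.1 | 0.5% | −0.2% |
| 0.2 | 2.0% | 1.0% |
| 0.3 | 4.6% | 4.0% |
| 0.4 | 8.3% | 7.9% |
| 0.6 | 20.0% | 18.1% |

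Values of r of 0.1–0.3 stand for a model that already holds a usable baseline TIR; 0.4–0.6 stand for one that does not.

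**The case against.** The strongest objection is that the article does not say the composite model is adjusted. A reader might infer that the weight-model list is carried over unchanged; the text says only that the modelling is similar, and the covariate set of a secondary model is commonly left to the SAP. This stands, and it makes the link problem conditional. If the composite model has arm terms only, the identity link does about as well as logit at day 84. At three visits the unadjusted identity fit was clean in 75% and 48% of trials, with no matching logit run. The link itself, however, is not left open: the article fixes it, in a passage that points back to an adjusted model.

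Further limits also stand. The counts combine non-convergence with fitted values outside 0–1, and one stray fitted value does not by itself spoil an arm difference. The response rates are assumed, and convergence depends on software and may differ in R, which the article specifies. Logit does not solve an empty arm. The Firth-penalized fit converged in all 9,000 simulated trials, but only as a plain day-84 logit model, not as a repeated-visit GEE.

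On HbA1c, a reader might infer that its omission biases the comparisons, especially as high HbA1c can lead to added drugs. The documents do not support this. Allocation is randomized, chance imbalance is already reflected in the confidence interval, and section 2.7 makes intensification optional: "Participants in this randomized clinical trial may start additional non‐randomized medication". Nor is there a case for HbA1c in the composite model. The simulated net gain was −0.1 to 0.3% at 25–50% drug uptake and 2.0–3.3% only at 75%.

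**Conclusion.** The concern holds in a conditional form and is minor. If the composite model is adjusted as the weight model is, the identity-link fit will usually fail or leave 0–1 at about 15 per arm: about 85–100% of simulated day-84 trials with the full list, against 3–20% for logit on the same list. These figures rest on assumed response rates and covariate effects. The large gap between the links rests less on the exact rates, because identity fits broke down across all the adjusted scenarios while logit fits failed only with an empty or full cell. A like-for-like logit run with the full list over three visits is not available.

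For TIR, leaving out baseline HbA1c is a modest efficiency loss: about 0–4% in standard error if a usable baseline TIR is in the model and about 8–18% if not, on assumed correlations. Nothing here contradicts the rest of the plan, biases an estimate or affects the primary outcome.

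**What to change.** In the SAP, for the composite:
- State whether the model is adjusted and, if so, by which covariates.
- Replace the identity link with a logit link in the GEE, keep the robust standard errors, and obtain the marginal risk differences and odds ratios by standardization.
- Name a fallback for a cell with no responders or only responders, such as a Firth-penalized logit model at day 84 with the same covariates. Day 84 is the time point at which section 2.4 defines the composite.

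For TIR, add baseline HbA1c as a continuous covariate in the MMRM.

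The cost is small. The SAP is not yet final, no new data are needed because HbA1c is already an entry criterion and a subgroup variable, and both promised composite measures are kept. In the TIR model HbA1c takes one degree of freedom, which widens the interval by about 1% if it predicts nothing.
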